### 2. Study process and implementation (see Fig. 2).

The study is scheduled to begin on 04/01/2021 and is planned to last for one year, but at least until the minimum number of cases (n) is reached.

After recruitment, randomization and inclusion in the study collective with electronic signing of the consent form, the study participants first complete the baseline questionnaire. After accessing the link and entering their individual password, the study participants can easily complete the study step by step from an Internet-enabled computer in the SoSci Survey online portal. When the number of cases reaches 2n, the study is terminated prematurely.

|                     | Registration    | Data acquisition | Intervention   | Data acquisition | Intervention   | Data acquisition | End              |
|---------------------|-----------------|------------------|----------------|------------------|----------------|------------------|------------------|
| Time                | t -1 | t 0   | t 1 | t 1   | t 2 | t 2   | t end |
|                     |                 |                  | Video          |                  | Video          |                  |                  |
| Registration        |                 |                  |                |                  |                |                  |                  |
| Eligibility         | x               |                  |                |                  |                |                  |                  |
| Consent             | x               | x                |                |                  |                |                  |                  |
| Group assignment    | x               |                  |                |                  |                |                  |                  |
| Intervention        |                 |                  |                |                  |                |                  |                  |
| Video               |                 |                  | A              |                  | B              |                  |                  |
| Video               |                 |                  | B              |                  | A              |                  |                  |
| Evaluation          |                 |                  |                |                  |                |                  |                  |
| Demographics        |                 | x                |                |                  |                |                  |                  |
| Primary endpoint    |                 |                  |                |                  |                | x                |                  |
| Secondary endpoints |                 |                  |                | x                |                | x                | x                |

**Fig. 2: Study procedure and organization of data collection**

The first part of the study with a short introduction, consent to participate in the study and answering the questions of the baseline questionnaire takes about 15 to 20 minutes. The time required for the second part of the study (main part with intervention) is also around 20 minutes for the test subjects (see Fig. 3).

[figure not shown]

**Fig. 3: respective time required for the two study sections**

In the main part of the study, the test subjects first watch a short explanatory film before being shown the two videos one after the other in a different order, depending on their study group (see Fig. 1). After watching the first video, they are asked to comment on it by answering identical questions in each group. The questions following the two videos viewed one after the other are also identical in the two groups. After all questions have been answered, the study is considered complete. Upon completion of the survey, parents are thanked for their participation in the study and asked to close the browser window.

**The following data on the study process will be collected:**

Number of parents approached, number of parents excluded (including reasons: declined to participate, exclusion criteria, other reasons), number of parents included and randomized to the respective scenarios, number of parents discontinuing the study, number of parents finally analyzed (including reasons for non-analysis). The same applies to female physicians.

**Data acquisition  $t_0$  (baseline questionnaire)**

As a basis of ensuring comparability and enabling subgroup analyses with regard to the primary and secondary endpoints of the study, sociodemographic data of the parents such as age, sex, sociocultural background (including language and religiosity/belief), highest educational attainment, employment, presence of medical expertise/knowledge, or medical background will be collected at baseline.

Since we assume that premature birth is a special life event for parents, they are asked how much they agree with the statement that the early birth of the child has changed their life, the family cohesion as well as the financial security of the family. To inquire about the influence of the premature birth on the family's instrumental resources, four items adapted from the "financial stress" subscale (F1-F4) of the Family Stress Questionnaire (FaBel questionnaire) were formulated. Also, when asking about changes in family cohesion, an item of the subscale "coping problems" (F12) of the same questionnaire is used. This is followed by questions about the family (marital status, number of children in the household) and information about the premature baby (date of birth, gestational age of the premature baby at birth, birth weight, multiple birth status, fertility treatment yes/no, severe cerebral hemorrhage yes/no).

In addition, with regard to the evaluation of outcome data after study inclusion, the following specific (personality) characteristics of parents and medical staff will be recorded:

- a. German version of the Brief Resilience Scale (BRS)
- b. The Optimism-Pessimism-2 Scale (SOP2)
- c. Herth Hope Index - German Version (HHI-D)
- d. Uncertainty Tolerance Scale (UGTS)
- e. Patient Health Questionnaire (PHQ 4)
- f. State-Trait Anxiety Inventory (STAI) Trate Scale.
- g. German short version of the State-Trait Anxiety Inventory Scale (STAI-SKD)

**Data acquisition  $t_1$  after the first video (A or B)**

Parents are asked to rate the degree of optimism of prognosis communication on a 7 point rating scale (1 = not at all optimistic to 7 = very optimistic).

- Parents' (state) anxiety is assessed using the German short version (5 items) of the State-Trait Anxiety Inventory (STAI-SKD) scale..
- Parental satisfaction with the way the clinician communicated the prognosis is assessed using a fully verbalized rating scale (range 1-7).
- The realism of parental assessment of prognosis is determined by the correlation between subjective assessment of the severity of prognosis (fully verbalized rating scale, range 1-7) and objective ability to reproduce the prognostic data conveyed. It will solicit a selection from percentages ranging from 0 to 100 percent in increments of ten (survival) or twenty-five (impairment).
- Parental level of optimism about the child's future (overall survival and survival without impairment) is assessed using a fully verbalized rating scale (range 1-7).
- A fully verbalized rating scale (range 1-7) is used to assess the degree of perceived hope (hopelessness).
- Using a fully verbalized rating scale (range 1-7), parents are asked whether they felt prepared to make a joint (treatment) decision with the physician in the announced follow-up interview.
- The general impression of the consulting physician on the parents is visualized by a fully verbalized rating scale (school grades 1 to 5, equal to the scale of the Professional Performance Questionnaire adapted to , sum score: 5-50) visualized.
- Physician professionalism is assessed using the German translation of a subscale of the Professional Performance Questionnaire (school grades 1 to 5, sum score: range 9 - 45 points) adapted from  determined.
- Physician compassion is assessed using the German translation of the Physician Compassion Questionnaire in a slightly modified version adapted from in a slightly modified version. The labels of the poles of the 5 items depicting the five dimensions of physician compassion were translated literally and back-translated by a native speaker, the scaling corresponds to a numerical rating scale with range 1-10.

**For physicians additionally:**

- In this case, the questionnaire *evaluation of a colleague* is used to evaluate the colleague according to .
- A fully verbalized rating scale (range 1-7) is used to self-assess the individual approach of the participating female physicians.

**Data acquisition  $t_2$  after the second video (B or A)**

- Parents are asked to rate the degree of optimism of prognosis communication on a 7-point rating scale (1 = not at all optimistic to 7 = very optimistic).
- Preference for video A or B (primary endpoint) is captured using a dichotomous question (1 = first video and 2 = second video).

**Data acquisition  $t_{end}$  on the completion of the study**

- Participants are explicitly asked about their preference for (rather) pessimistic or (rather) optimistic communication of forecasts (fully verbalized 7-point rating scale with 1 = not at all optimistic to 7 = very optimistic).
- Parents are asked to provide an assessment regarding the importance of doctor-parent discussions in general and certain discussion content (transmission of prognostic data) in particular (4 items each and a fully verbalized 5-point rating scale with 1 = strongly disagree to 5 = strongly agree).
- Parents indicate whether they feel burdened by study participation in general or by watching the videos in particular (2 items and a 5-point rating scale with 1 = not at all to 7 = very much).

- Parents are informed that the study team is planning further research projects involving parents of former preterm infants in the future. Parents are invited to express their interest in participating in future studies by contacting the study team directly by e-mail.
- Physicians have the opportunity to comment on difficulties in communicating prognoses in everyday clinical practice. A free text field is available for this purpose.

**3. Rules for discontinuing the research project for the individual, as well as for the entire study**

Only very low study-related risks are assumed for the test subjects (minimal risk). Individual subjects may discontinue the study at any time, e.g. if dealing with the subject matter is too emotionally stressful. In this case, a psychological consultation will be offered. If more than 50% of the subjects drop out of the study, the entire study will be terminated. This evaluation is carried out for every 20 subjects included.

## **VI. Statistics**

### **1. Sample size calculation**

Simplifying, the resulting number of cases is used as the number of parent pairs to be recruited, where one or both parents may consent. Tested the null hypothesis of balanced preference, period-corrected, with a chi quadrat test for independence in the four-field table defined by sequence and 'preference for video B vs. video A'. To detect an effect corresponding to the 3:2 preference ratio with a power of 80%, in the absence of a period effect, 194 families with evaluable data from at least one parent are needed. Assuming a significant period effect, the same treatment effect in sequence AB could result in a preference for video 1 with a probability of 0.50, whereas in sequence BA it would be 0.3077. The required number of cases would then be 204. Assuming that only one parent participates per family and that the dropout rate is 5%, 215 families would have to be recruited. At least 153 families would have to be recruited if both partners always participate and the agreement in the assessment corresponds to a kappa of 0.5. After inclusion of 50 to 70 families, a reassessment of the number of cases will be scheduled.

### **2. Statistical evaluation methods**

The analysis of the primary endpoint 'preference B over A' is done by fitting a marginal logistic model with the endpoint 'second video was preferred' using the method of generalized estimating equations. For this purpose, parents are considered as clusters of scope 1 or 2. The exponentiated halved coefficient of the factor 'sequence' (A then B coded as 0, B then A coded as 1) is used as the period-corrected estimate of the odds for preference of intervention A. The test of the null hypothesis is performed as a Wald chi quadrat test at the two-tailed level 0.05.

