### **3. Description of the randomization method**

The concealment of allocation is performed in blocks of variable length, stratified into the three strata 'participation of mother only', 'participation of father only', 'participation of both parents'. Allocation will be done after recruitment of the parents by an employee of the University Medical Center of the Johannes Gutenberg University Mainz not involved in the acquisition outside the online acquisition software and will be done in the order of consent. Both parents receive the same allocation in each case.

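### The primary GEE names only sequence although randomization is stratified by mother only, father only or both parents; adding the strata is a small, nearly free gain in efficiency

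*Protocol*

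**What the plan says.** Protocol VI.2 (Statistical evaluation methods) describes the primary analysis as "fitting a marginal logistic model with the endpoint 'second video was preferred' using the method of generalized estimating equations". Families are the clusters: "parents are considered as clusters of scope 1 or 2". The estimate comes from one term: "The exponentiated halved coefficient of the factor 'sequence' (A then B coded as 0, B then A coded as 1"). Half of that coefficient, exponentiated, is reported as a period-corrected odds of preference. The test is "performed as a Wald chi quadrat test at the two-tailed level 0.05". No other model term is named.

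Protocol VI.3 (Description of the randomization method) says that allocation is "stratified into the three strata 'participation of mother only', 'participation of father only', 'participation of both parents'", in blocks of variable length, and adds: "Both parents receive the same allocation in each case". The summary of study procedures (III.1) gives the purpose, which is to spread couples and single participating parents evenly over the two groups. The protocol neither puts the strata into the primary model nor says that they are left out.

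**The concern.** An analysis would normally reflect the factors used to balance the randomization. Here the reason is specific to the outcome. Because the response is whether the second video was preferred, the intercept carries the order effect and the sequence coefficient carries twice the log-odds of preferring A. One intercept corrects for one common order effect. If mothers alone, fathers alone and couples differ in their pull towards the first or second video, that difference is a stratum main effect.

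Sequence is balanced within strata, so this between-stratum variation does not disturb the sequence comparison. A model without strata still counts it as noise in the standard error. The robust GEE variance does not remove it: clustering by family handles correlation within couples, not differences between strata. At stake is some power, in a plan that sizes its one-parent case close to 80%.

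**Working it through.** **1. The plan's own figures.** Section VI.1 states: "To detect an effect corresponding to the 3:2 preference ratio with a power of 80%, in the absence of a period effect, 194 families" are needed. With a period effect it assumes "a preference for video 1 with a probability of 0.50, whereas in sequence BA it would be 0.3077". The formula per sequence is n = [1.96·√(2p̄q̄) + 0.8416·√(p₁q₁ + p₂q₂)]² / (p₁ − p₂)².

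- 0.6 against 0.4: (1.3859 + 0.5831)² / 0.04 = 96.9, so 97 per sequence and 194 in total.
- 0.5 against 0.3077: (1.3601 + 0.5727)² / 0.03698 = 101.0, rounded up to 102 per sequence and 204 in total.
- 204 / 0.95 = 214.7, so 215. For couples with kappa 0.5: 204 × 1.5 / 2 = 153.

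All four figures reproduce.

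**2. The plan's period effect on the model scale.** P(second preferred) is 0.50 in AB and 1 − 0.3077 = 0.6923 in BA. The logits are 0 and 0.811. Their difference, 0.811 = 2·ln 1.5, is the sequence coefficient. Their mean, 0.405, is the period log-odds, which corresponds to P(second preferred) = 0.60.

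**3. Inputs that the protocol does not give (assumed).** Period log-odds by stratum (mother/father/both); stratum shares of equal thirds or 0.40/0.10/0.50; 1:1 allocation. For the analytic check: 204 families, one observation each, stratum-level odds 1.5, exact balance within strata. Standard errors refer to the sequence coefficient before halving.

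**4. Formulas.** With n = 102 per sequence, stratum shares w, stratum probabilities p and their weighted mean m in each sequence:

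- Model variance, sequence only: Σ over sequences of 1 / [n·m(1 − m)].
- True variance under balance within strata: Σ over sequences of Σw·p(1 − p) / [n·(m(1 − m))²].
- Variance with strata in the model: 1 / Σ n·w·v₀v₁/(v₀ + v₁), where v = p(1 − p) in each sequence.

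**5. Worked case: -0.8/0.4/0.8, equal thirds.**

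- AB: p = 0.2305, 0.4986, 0.5974; m = 0.4422; m(1 − m) = 0.2467; mean p(1 − p) = 0.2226.
- BA: p = 0.4026, 0.6911, 0.7695; m = 0.6211; m(1 − m) = 0.2353; mean p(1 − p) = 0.2105.
- Model SE = √(0.0398 + 0.0417) = 0.285.
- True SE = √(0.0359 + 0.0373) = 0.270.
- Sequence-only coefficient = 0.7265, so odds = exp(0.363) = 1.44.
- Power, sequence only: Φ[(0.7265 − 1.96 × 0.2853) / 0.2704] = Φ(0.62) = 73%.
- With strata: SE = 0.3035; power Φ(0.8109/0.3035 − 1.96) = Φ(0.71) = 76%.

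**6. Results.** Each range covers the two sets of shares.

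| Period log-odds | Power, sequence only | Power, with strata | Type I error, sequence only |
|---|---|---|---|
| 0.4/0.4/0.4 | 79.4% | 79.4% | 0.050 |
| 0.405/0.405/0 | 79.7–79.9% | 79.9–80.2% | 0.049 |
| 0/0.4/0.8 | 76.9–77.8% | 77.7–78.4% | 0.046–0.047 |
| -0.8/0.4/0.8 | 71–73% | 75–76% | 0.036–0.038 |

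In the last row the true SE is 0.266–0.270 against a model SE of 0.285.

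**7. Check with couples.** Simulated GEE with an independence working correlation and robust SE: 204 families, shares 0.35/0.10/0.55, blocks of 4 or 6, kappa 0.5, 4,000 to 10,000 runs. Entries are sequence only against sequence plus strata.

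| P(second preferred) by stratum | Type I error | Power |
|---|---|---|
| 0.5/0.5/0.5 | 0.053 vs 0.053 | 87.7% vs 87.7% |
| 0.6/0.6/0.5 | 0.048 vs 0.050 | 86.1% vs 86.3% |
| 0.6/0.5/0.4 | 0.050 vs 0.054 | 85.0% vs 85.8% |
| 0.7/0.5/0.3 | 0.037 vs 0.050 | 78.2% vs 81.4% |
| 0.8/0.5/0.2 | 0.023 vs 0.047 | 60.2% vs 71.4% |

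The direction is the same. The loss becomes large only when the order effect reverses strongly between strata.

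**The case against.** The strongest reply is that nothing here is stated wrongly. VI.2 does not exclude the strata, covariates are often settled in the SAP, and the SAP is not to hand. It may already add them. That stands as a limit. But VI.2 fixes outcome, coding, estimator, clustering and test in detail, so the model as written is sequence only and can be commented on.

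A second reply is that the loss is trivial at the scale the protocol contemplates. That also stands. Its own period effect is about 0.4 on the log-odds scale, and if some strata have it and others none, the cost is about 0.2 power points. The -0.8/0.4/0.8 case needs P(second preferred) of 0.31 in one stratum and 0.69 in another, a reversal that nothing in the protocol suggests. Section III.1 expects the two parents to respond differently to such conversations, but that does not show that order effects differ.

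A reader might also infer that leaving out the strata biases the odds towards 1, since 1.44 is below 1.5. The protocol does not support that reading. VI.2 specifies a marginal model, and 1.44 is the correct marginal odds in that scenario. The gap to 1.5 is non-collapsibility of the odds ratio: two different estimands, not an error in one of them. Nor can one infer a risk of false positives, because the sequence-only test errs on the cautious side.

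**Conclusion.** The point holds as a minor efficiency matter. The sequence-only test is valid. It is conservative to the extent that order effects differ between strata, and not at all if they are equal. At 204 families with one parent each, the cost is about 0.2 power points when some strata have the protocol's own period effect and others none, under 1 point at 0/0.4/0.8, and about 3 to 4 points at -0.8/0.4/0.8. In that last case the model SE overstates the true SE by roughly 5 to 7% (0.285 against 0.266–0.270).

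These sizes rest on assumed shares and order effects. Couples add data beyond the one-parent case (87.7% simulated power with no order-effect differences), so a loss need not take the trial below 80%. A positive result from the analysis as written would not be in doubt.

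**What to change.** In VI.2, add the randomization stratum (two indicators) to the marginal logistic GEE. Keep the sequence coding, family clustering, two-sided Wald test and exp(beta/2). State that the reported odds are then conditional on stratum.

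The cost is one sentence and a small change of estimand: the odds are no longer fully marginal, which should be said wherever they are reported. Where strata did not differ, adding the terms cost no power in the checks above. If the SAP already includes the strata, it is enough to align the wording of VI.2 with it.

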### **3. Description of the randomization method**

The concealment of allocation is performed in blocks of variable length, stratified into the three strata 'participation of mother only', 'participation of father only', 'participation of both parents'. Allocation will be done after recruitment of the parents by an employee of the University Medical Center of the Johannes Gutenberg University Mainz not involved in the acquisition outside the online acquisition software and will be done in the order of consent. Both parents receive the same allocation in each case.

## VII Ethical and legal aspects

1. The study is conducted in accordance with currently valid national and international ethical and legal standards. The Declaration of Helsinki in its latest German version will be observed. The study protocol and substantial amendments will be registered with [clinicaltrials.gov](https://www.clinicaltrials.gov) and the German Registry of Clinical Trials (DRKS) before the start of the study. The legal basis for the protection of personal data is the European Data Protection Regulation (DS-GVO). Personal data will only be processed after an effective declaration of consent (Art. 6 para. 1 letter c) DSGVO).

The patient data are first collected digitally on the questionnaire. Subsequently, a code is assigned to each patient. The data is stored digitally by means of the patient code. The collection and storage of study-related data is thus exclusively in pseudonymized form.

2. **Information on the purpose and potential benefits or risks of the study.**

The research project serves a purely scientific objective. In the long term, the study results should help to increasingly take into account individual parental needs and preferences with regard to physician-parent communication in neonatology and to strengthen parent-centered care in this special and particularly challenging specialty.

Some parents of preterm infants describe their child's premature birth as a life-changing experience that requires them to reinvent themselves as parents and rewrite their own story. Physicians should and can support parents in this process: through medical expertise and through successful communication. It is likely that the way medical information is communicated can influence parents' lived experience. The findings of this study should help to orient future communication in the context of uncertainty more towards the individual needs and preferences of parents as representatives of their children and direct experiencers and thus contribute to improving the quality of care in neonatology.

Parents of former preterm infants can help in this process thanks to their own lived experience of preterm birth and the accompanying life transformation. This research project wants to draw attention to the importance of communication in the context of uncertainty on the one hand, and to the involvement of "former parents" in research projects on the other hand. It would be desirable in the near future to involve parents even more in neonatology or pediatric research in general and to do research with them rather than just about them. There are already concepts and scientific findings for the active involvement of "resource veteran parents" not only in research, but also in clinical care or teaching.

